## 5. STUDY DESIGN

### 5.1 STUDY TYPE & DESIGN & SCHEDULE

#### 1. Trial design

Randomised controlled trial.

#### 2. Cohort:

---

**Study Name:** A randomized trial of focused cardiac, lung, and femoral and popliteal vein ultrasound on the length of stay in internal medicine admissions with a cardiopulmonary diagnosis – the IMFCU 1 study

**Protocol Number:** 2018.200

**Version & date:** version 1 dated 20 May 2018

Page 10 of 18

- a. Adult participants  $\geq 18$  years will be included if they can provide informed consent and are admitted to an internal medicine unit at the Royal Melbourne Hospital with a cardiopulmonary diagnosis and are expected to remain in hospital  $> 24$  hours.
  - b. Exclusion: Participants will be excluded if they have already been admitted  $> 24$  hours, are admitted for social rather than medical reasons, are unable to provide consent, are on contact or respiratory isolation, or have received a transthoracic echocardiogram within 4 weeks prior to admission, or a CT chest scan during the admission process prior to enrolment.
- 3. Location: Single-centre at the Royal Melbourne Hospital
- 4. The primary outcome will identify whether the ultrasound examinations leads to a meaningful reduction in length of stay. The secondary outcomes are designed to identify mechanisms to explain an effect if observed, such as the incidence of new diagnoses which were missed by clinical evaluation and the number of tests required prior to the definitive diagnosis being established.
- 5. Measurements – all measurements are re-identifiable
  - a. Demographic information including gender, age, height and weight, prior medical conditions, medications, admission diagnosis
  - b. Diagnosis information including the initial differential diagnosis, alternative diagnosis and the definitive diagnosis.
  - c. Times including hospital length of stay, time to definitive diagnosis
  - d. Investigations performed (type and number of tests)
    - i. Imaging such as X-ray, CT, MRI, nuclear medicine and ultrasound including echocardiography
    - ii. Pathology tests such as blood tests, urine tests, bacterial cultures or viral swabs.
  - e. Cardiac, lung and vein pathology identified on the focused cardiac, lung, and femoral and popliteal vein ultrasound (intervention group only)
- 6. Data collection and handling
  - a. Data will be collected through interview and extracted from hospital records.
  - b. The treating medical staff (at least registrar level) will complete a custom diagnostic and management form on a daily basis (see CRF). Change in the custom form fields will be used to identify change.
  - c. The number and type of tests will be identified from hospital records including online pathology and radiology services.

- d. The definitive diagnosis will be reported by the treated medical team. The diagnosis will be verified against the discharge diagnosis.
  - e. All FCU lung, and femoral vein ultrasound images will be recorded in DICOM format. The images and report forms will be checked by an independent expert, as a quality assurance of the accuracy of the bedside ultrasound. Furthermore, if the participant undergoes comprehensive echocardiography or lung ultrasound or CT scan, the finding of the bedside examination will be cross checked against the formal investigations.
7. Time frames: participants will be enrolled within 24 hours of hospital admission and follow up concludes at hospital discharge.
  8. No home visits

This protocol will be used as part of a Master of Medicine degree for [name] [name] at the University of Melbourne.

9. Provide a flowchart or table specifying visits, interventions and other relevant details

### **STUDY TABLE**

| Example procedures | Assessment/Procedure                                       | Within 24 hr of admission (Day 1) | Day 2 | Day 3 and | Discharge day |
|---------------------------|------------------------------------------------------------|-----------------------------------|-------|-----------|---------------|
|                           | Informed Consent                                           | x                                 |       |           |               |
|                           | Demographic Information                                    | x                                 |       |           |               |
|                           | Admission diagnosis and management plan                    | x                                 |       |           |               |
|                           | FCU, Lung and femoral and popliteal vein scan is allocated | x                                 |       |           |               |
|                           | Diagnosis, management and investigations form              | x                                 |       |           | x             |

## 5.2 STANDARD CARE AND ADDITIONAL TO STANDARD CARE PROCEDURES

| Standard Care Procedures            |                                        |               | Additional To Standard Care                                     |                                          |               |
|-------------------------------------|----------------------------------------|---------------|-----------------------------------------------------------------|------------------------------------------|---------------|
| Procedure                           | Time/Visit                             | Dosage/Volume | Procedure                                                       | Time/Visit                               | Dosage/Volume |
| Clinical Evaluation by medical team | Daily until discharge                  | NA            | Focused Cardiac, Lung and femoral and popliteal vein Ultrasound | Within 24 hours of admission to hospital | NA            |
| Investigations                      | As determined by treating medical team | NA            |                                                                 |                                          |               |
|                                     |                                        |               |                                                                 |                                          |               |

## 5.3 RANDOMISATION

Randomisation is performed using internet software (<https://www.sealedenvelope.com/simple-randomiser/v1/lists>) in unequal block sizes of 4, 6 and 8. Allocation will be concealed in double sealed opaque envelopes. Allocation is revealed after informed consent is obtained by the researcher. The researcher is not blinded to allocation as the intervention (FCU, Lung, and femoral and popliteal ultrasound) is only performed in the intervention arm and cannot be blinded. Outcome data including length of stay or diagnostic and management decisions are determined by the treating medical staff and not under the influence of the investigators.

## 5.4 STUDY METHODOLOGY

This study will allocate participants to receive focused cardiac, lung, and femoral and popliteal ultrasound within 24 hours of admission (or not). All other aspects of care, including investigations performed, treatments provided and discharge planning is determined by the treating medical team. The intervention will provide additional information to the treating team only, with no direction about management, in keeping with a pragmatic trial design.

The intervention is focused cardiac, lung, and femoral and popliteal ultrasound, performed in accordance with the University of Melbourne Ultrasound Education Group training methods [ref]. The investigator will perform the ultrasound examinations and report these on the

---

**Study Name:** A randomized trial of focused cardiac, lung, and femoral and popliteal vein ultrasound on the length of stay in internal medicine admissions with a cardiopulmonary diagnosis – the IMFCU 1 study

**Protocol Number:** 2018.200

**Version & date:** version 1 dated 20 May 2018

Page 13 of 18

iHeartScan and iLungScan report forms (University of Melbourne). **No index entries found.** See Appendix. The investigators are trained and competent to perform the examinations. All ultrasound examinations will be stored in DICOM format and checked by an expert investigator.

A diagnostic and management form (See CRF) will be completed before and after the ultrasound examination by the treating medical team. All other data is extracted from the hospital records and electronic databases.

## **6. STUDY POPULATION**

### **6.1 RECRUITMENT PROCEDURE**

Potential participants will be identified from hospital admissions data within the preceding 24 hours. Specifically, the participants will have an initial admission diagnosis of “cardiopulmonary”, and be admitted to one of the general medicine units (AMU, Gen Med 1-3)

#### *Inclusion Criteria*

Adult participants  $\geq 18$  years will be included if they can provide informed consent and are admitted to an internal medicine unit at the Royal Melbourne Hospital with a cardiopulmonary diagnosis and are expected to remain in hospital  $> 24$  hours.

### **6.2 EXCLUSION CRITERIA**

Participants will be excluded if they have already been admitted for  $> 24$  hours, are admitted for social rather than medical reasons, are unable to provide consent, are on contact or respiratory isolation, or have received a transthoracic echocardiogram within 4 weeks prior to admission, or a CT chest scan during the admission process prior to enrolment.

### **6.3 CONSENT**

Individual written informed consent will be obtained.

## **7. PARTICIPANT SAFETY AND WITHDRAWAL**

### **7.1 RISK MANAGEMENT AND SAFETY**

The focused cardiac, lung and femoral vein ultrasound is a non-invasive procedure. The ultrasound is placed on the participants chest or leg with firm pressure and the scans take approximately 15 minutes to perform. The participant will be asked to lie on their left side and to sit up during the examination. The ultrasound itself does not pose any danger to the patient.

### **7.2 HANDLING OF WITHDRAWALS**

Participants will be informed that they are free to withdraw from the study at any time. They will also be informed that their withdrawal will not affect the relationship between them and the treating doctors or the hospitals. They will be informed that any data collected to point of withdrawal will be used to prevent bias in the results, unless they specifically refuse that request. From the time of withdrawal, no further data will be acquired for that participant.

### 7.3 REPLACEMENTS

We will not replace withdrawn participants. Rather, we have increased the sample size for the study to account for withdrawals.

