| Safety considerations:      | The focused cardiac, lung and vein ultrasound is non-invasive and does not present risk to the patient                                                                                                                                                                                                                                                                                                                                                                                                                                                                                                                                                                                                                                                                                                                               |
| Statistical Methods:        | 
The outcome of interest, hospital length of stay (LOS), is expected to be skewed and hence will be log transformed for the purposes of analysis. Control data were available for Q4 2017, with a mean log based 10 LOS of 2.01 (equivalent to 103 hours on the original scale) and a standard deviation of 0.36. In this study censoring will not be applied to the LOS. The primary outcome will be tested using Student t-test on the log-transformed LOS data.
 
In order to detect a clinically important reduction in LOS of 24 hours for the ultrasound group, based on the expected control value above and a common standard deviation on the log scale, power of 0.8 and size 0.05, 122 participants are required in each of the two treatment groups, which will be rounded up to a total of 250 participants.
 |

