### 8.2 POWER CALCULATIONS

The outcome of interest, hospital length of stay (LOS), is expected to be skewed and hence will be log transformed for the purposes of analysis. Control data was available from 2017, with a mean log based 10 LOS of 2.01 (equivalent to 103 hours on the original scale) and a standard deviation of 0.36.

In order to detect a clinically important reduction in LOS of  $\geq 24$  hours for the ultrasound group, based on the expected control value above and a common standard deviation on the log scale, power of 0.8 and size 0.05, 122 patients are required in each of the two treatment groups, which will be rounded up to a total sample size of 250 participants.

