## **Statistical analysis plan -IMFCU study**

Statistical analysis will be performed using the software SPSS version 27 (Statistical Package for the Social Sciences).

Distribution of demographic and baseline characteristics between groups will be analysed using Fisher test for categorical data and Student's t-test for ordinary data.

The primary outcome, length of hospital stay in hours, will be analysed using Student's t-test on log-transformed data to normalize skewed data and following an intention-to-treat approach. A cut-off of 30 days will be applied to avoid the effect of excessively extended hospital stays. Significance was defined as  $p < 0.05$ . For patients who died in the hospital, death will be treated as hospital discharge for the primary analysis as the unpublished mortality rate for patients admitted to internal medicine wards at the Royal Melbourne Hospital is low (2.7%). Patients with missing data will not be included in the primary statistical analysis.

Because the introduction of Focused Clinical Ultrasound (FCU) was new to the internal medicine unit, we hypothesised that there would be a lead-in period where the FCU findings may not be accepted by the treating team, whereas as the physicians became more familiar with FCU, the finding would be more trusted and more likely to be acted upon. A sensitivity analysis will be performed on outcomes to compare the first half versus the second half of the participants.

The primary outcome will be analysed in pre-defined subgroups that we suspect a stronger effect of FCU: older than 75 years old, history of chronic heart failure, history of chronic obstructive pulmonary disease and patients with multiple comorbidities.

Secondary outcomes will be analysed using parametric or non-parametric tests according to the type of data. All estimates will be reported with 95% confidence intervals.

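### Section 7.3 says the sample size was raised for withdrawals, but 250 is 244 rounded up (a 2.4% margin with no stated rate), and withdrawal before discharge loses the primary outcome

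*Protocol*

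**What the plan says.** Section 7.3 states that withdrawn participants will not be replaced and gives this reason: "Rather, we have increased the sample size for the study to account for withdrawals".

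The sample size is derived in two places, the synopsis and section 8.2. Section 8.2 starts from control data "with a mean log based 10 LOS of 2.01 (equivalent to 103 hours on the original scale) and a standard deviation of 0.36", a 24-hour reduction and "power of 0.8 and size 0.05", and concludes: "122 patients are required in each of the two treatment groups, which will be rounded up to a total sample size of 250 participants". The synopsis says the same: "122 participants are required in each of the two treatment groups, which will be rounded up to a total of 250 participants". Neither contains a withdrawal rate or a withdrawal term, and no rate appears elsewhere in the document.

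Section 7.2 says that data gathered before withdrawal will be used, to prevent bias, unless the participant refuses. It then adds: "From the time of withdrawal, no further data will be acquired for that participant".

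Section 4.3 measures the primary outcome, length of stay (LOS), up to discharge from hospital. Section 5.1 ends follow-up at discharge.

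The statistical analysis plan at the end of the document calls the primary analysis intention-to-treat and, in the same paragraph, states: "Patients with missing data will not be included in the primary statistical analysis".

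**The concern.** Two things do not fit together.

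First, section 7.3 relies on an allowance for withdrawals to justify not replacing them. The only place such an allowance could be is the step from 244 to 250, and section 8.2 calls that step rounding. A reader of 7.3 would believe that a withdrawal rate had been considered and covered.

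Second, LOS is complete only at discharge. If nothing is acquired after withdrawal, a participant who withdraws earlier has no LOS, and the rule on missing data then removes that participant. The primary analysis becomes complete-case on the outcome, although it is labelled intention-to-treat. Allocation is revealed after consent, the researcher is not blinded, and only one arm is scanned (section 5.3), so withdrawal after allocation could differ between arms. The loss is largely avoidable, because the protocol already draws on hospital records for its data (sections 5.1 and 5.4).

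**Working it through.** **Inputs.** Control LOS 103 h, SD 0.36 on the log10 scale, reduction 24 h, power 0.8, size 0.05, two equal groups, 122 per arm, total 250 (synopsis and section 8.2). Sidedness is not stated. Withdrawal rate is not stated, so the 5% and 10% used below are assumptions.

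**1. Reproduce 122.**
- Effect on the log10 scale: log10(103) − log10(79) = 2.0128 − 1.8976 = 0.1152.
- Standardised effect: 0.1152 / 0.36 = 0.320.
- Normal approximation, n per arm = 2 × ((z for size + z for power) / 0.320)². One-sided: 2 × ((1.645 + 0.842) / 0.320)² = 120.7, so 121.
- Solved exactly for the t-test, one-sided: 121.4, so 122. This is the plan's figure.
- Two-sided t-test: 154.2, so 155. This does not reproduce 122.
- Starting from 10^2.01 = 102.3 h instead of 103 h, the one-sided t-test needs 119.6, so 120.

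The 122 is therefore reached with no withdrawal term.

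**2. Size of the surplus.**
- 2 × 122 = 244, and 250 − 244 = 6.
- 250 × (1 − w) ≥ 244 requires w ≤ 6/250 = 2.4%.

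**3. Power if patients are lost** (t-test, standardised effect 0.320, one-sided 0.05, the basis that gives 122).

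| Loss | Analysed | Per arm | Power |
|---|---|---|---|
| none | 250 | 125 | 0.810 |
| 2.4% | 244 | 122 | 0.802 |
| 5% (assumed) | 237.5 | 118.75 | 0.792 |
| 10% (assumed) | 225 | 112.5 | 0.773 |

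Against the planned 0.80, the shortfall is under 1 point at 5% and about 3 points at 10%.

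**4. What a real allowance would look like.** Inflating by 122 / (1 − w):
- 5%: 122 / 0.95 = 128.4, so 129 per arm, 258 in total.
- 10%: 122 / 0.90 = 135.6, so 136 per arm, 272 in total.

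**5. Following a withdrawn participant through the text.**
- LOS ends at discharge (section 4.3).
- Acquisition stops at withdrawal (section 7.2), so withdrawal before discharge leaves no LOS.
- The analysis plan omits patients with missing data from the primary analysis.
- It follows that this participant is not analysed in the allocated arm. No single sentence says so; it results from combining the three. Section 7.2's aim of using earlier data to prevent bias has no effect on the primary outcome, since the data up to that point contain no discharge time.

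**The case against.** There are several fair points in favour of the plan.

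- **A surplus does exist.** 250 exceeds 244, so it goes too far to call section 7.3 false. This stands: the supportable statement is that the allowance is unquantified and at most 2.4%. Nor does the document show that 2.4% is too little. The scan takes about 15 minutes (section 7.1), follow-up ends at discharge, and the expected control stay is about 103 h.
- **Withdrawals do not explain low power.** A reader who assumes a two-sided test might quote about 0.69 at 5% loss and 0.67 at 10% and blame withdrawals. Two-sided power is already 0.71 with all 250 analysed, so most of that shortfall comes from the unstated sidedness, which is a separate matter.
- **The missing-data sentence need not cover other variables.** One might infer that a patient with a known LOS is excluded for a missing baseline item. The sentence closes the paragraph on the primary outcome, and an unadjusted t-test needs only arm and LOS. Missing LOS is the natural reading.
- **Intention-to-treat can mean analysed as randomised where the outcome exists.** This is a common usage. It softens the conflict but leaves the outcome uncollected for withdrawn participants, and the plan does not say that this is what it means.
- **Stopping data at withdrawal is a legitimate consent policy.** Agreed, and participants may refuse further access, so some LOS values may still be lost. The consent pages are not available here, so what they allow cannot be judged.

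None of this supplies the withdrawal allowance that section 7.3 says was made.

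**Conclusion.** The point holds in a limited form. Section 7.3 claims an increase that the synopsis and section 8.2 do not contain. The only margin is 6 patients, or 2.4%, produced by rounding and with no rate behind it. The consequence for power is modest: about 0.79 at 5% loss and 0.77 at 10%, given the plan's own effect and SD, the one-sided test that reproduces 122, and withdrawal rates that are assumed.

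The more useful reason to act is the avoidable loss of the primary outcome. That withdrawn participants drop out of the primary analysis is a sound inference from section 7.2 and the analysis plan, not something either states. A reader might go further and conclude that the comparison will be biased. The documents do not support that: they give no withdrawal rate, overall or by arm, so neither the direction nor the size of any bias is known. What can be said is that the trial is unblinded and the plan leaves this risk open when it could be reduced cheaply.

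**What to change.** - **Section 7.3:** delete the claim, or state that 250 leaves a margin of 6 patients (2.4%) over the 244 required.
- **Section 7.2 and the consent form:** provide that when a participant stops study procedures, admission and discharge times and discharge status are still taken from hospital records unless the participant refuses.
- **Statistical analysis plan:** state that all randomised participants with a recorded LOS are analysed in their allocated arm, and report the number without LOS by arm. This is still complete-case on LOS. The gain comes from having fewer missing values and from making the remaining ones visible.

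The cost is wording changes and a minor ethics amendment. No extra patients are needed.

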## 8. STATISTICAL METHODS

### 8.1 SAMPLE SIZE ESTIMATION & JUSTIFICATION

The sample size estimates and statistical methods has been written by our consulting statistician, [name], from the University of Melbourne Statistical Centre.

### 8.2 POWER CALCULATIONS

The outcome of interest, hospital length of stay (LOS), is expected to be skewed and hence will be log transformed for the purposes of analysis. Control data was available from 2017, with a mean log based 10 LOS of 2.01 (equivalent to 103 hours on the original scale) and a standard deviation of 0.36.

In order to detect a clinically important reduction in LOS of  $\geq 24$  hours for the ultrasound group, based on the expected control value above and a common standard deviation on the log scale, power of 0.8 and size 0.05, 122 patients are required in each of the two treatment groups, which will be rounded up to a total sample size of 250 participants.

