### 8.3 STATISTICAL METHODS TO BE UNDERTAKEN

No censoring will be used for length of hospital stay. The primary outcome will be analyzed using Student's t-test on the log transformed LOS data in hours. Secondary outcomes will be analysed using parametric or non-parametric tests according to the type of data, whether the data is skewed, and whether repeated measures are used. For secondary endpoints, significance will be defined as  $p < 0.01$  to reduce the risk of Type 1 error.

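### The 122 per group matches only a one-sided 5% test; for the two-sided analysis that is planned, power is about 71%, not 80%

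*Protocol*

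**What the plan says.** Section 8.2 takes its control data from 2017: "mean log based 10 LOS of 2.01 (equivalent to 103 hours on the original scale) and a standard deviation of 0.36". The target in the Synopsis is a "clinically important reduction in LOS of 24 hours for the ultrasound group". The calculation is "based on the expected control value above and a common standard deviation on the log scale", and section 8.2 then gives this result: "power of 0.8 and size 0.05, 122 patients are required in each of the two treatment groups". The planned enrolment is 250 in all. The Synopsis repeats the result: "power of 0.8 and size 0.05, 122 participants are required in each of the two treatment groups".

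For the analysis, section 8.3 specifies a Student's "t-test on the log transformed LOS data in hours". The statistical analysis plan at the end of the protocol repeats this test, sets significance at p < 0.05 and adds: "All estimates will be reported with 95% confidence intervals". Neither text uses the word one-sided or two-sided.

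**The concern.** A size of 0.05 does not fix a sample size until the sidedness is known. Here it is not stated, and the figure given matches one choice while the analysis text points to the other. An unqualified t-test at p < 0.05 with 95% intervals is a two-sided 5% analysis. A one-sided 5% test would correspond to a 90% interval.

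The figure at stake is the power for the primary endpoint. The study question is whether ultrasound shortens stay by at least 24 hours. If the trial finds no difference, readers will judge that result by the stated 80% power for 24 hours, and they would be giving it more weight than the design supports. Leaving the sidedness open also means it could be settled after the data are seen, which would matter if the two-sided p-value fell between 0.05 and 0.10.

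**Working it through.** **Inputs** (Synopsis and section 8.2): control 103 h, reduction 24 h, so 79 h with ultrasound; common SD 0.36 on the log10 scale; power 0.80; size 0.05; two equal groups. With 250 patients in total there are 125 per group.

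**Effect on the analysis scale**

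- Difference: log10(103/79) = 0.1152
- Standardised difference: d = 0.1152/0.36 = 0.320

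**Reproducing the plan's figure.** The normal approximation is n per group = 2(z_alpha + z_power)²/d², with z_power = 0.842 for 80% power.

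- One-sided 5%: 2(1.645 + 0.842)²/0.320² gives 121 after rounding up. The exact noncentral t calculation gives 121.4, so **122**, which is the protocol's number.
- Two-sided 5%: 2(1.960 + 0.842)²/0.320² gives 154 after rounding up. The exact t calculation gives 154.2, so **155**.

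**Power of the two-sided test at the planned size.** The normal approximation is power = Φ(d√(n/2) − 1.960).

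- n = 122: Φ(2.500 − 1.960) = 70.5%; exact t 70.2%
- n = 125: Φ(2.530 − 1.960) = 71.6%; exact t 71.2%

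The mean of 2.01 back-transforms to 102.3 h rather than 103 h, so both control values were tried (exact t):

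| Control value | Difference (log10) | One-sided n | Two-sided n | Two-sided power, 122 per group | Two-sided power, 125 per group |
|---|---|---|---|---|---|
| 103 h | 0.1152 | 121.4 | 154.2 | 70.2% | 71.2% |
| 102.3 h | 0.1161 | 119.6 | 152.0 | 70.8% | 71.9% |

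**Could rounding of the inputs explain 122?** Varying the mean over 2.005 to 2.015 and the SD over 0.355 to 0.365 gives a two-sided n of 144 to 160 (normal approximation), and two-sided power at 122 per group of 69% to 74%. A two-sided n of 122 would need an SD of about 0.32 or a reduction of about 26.5 h. The documents give neither.

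**What 125 per group does detect.** For two-sided 80% power the exact t calculation needs d = 0.3558. The log10 difference is then 0.3558 × 0.36 = 0.1281, the ratio is 10^(−0.1281) = 0.745, and the reduction from 103 h is about 26.3 h.

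**Margin.** 250 − 2 × 122 = 6 patients, or 2.4% of 250. Section 7.3 says the sample size was increased to allow for withdrawals, and the statistical analysis plan leaves patients with missing data out of the primary analysis. Losing those 6 brings two-sided power back to about 70%. As an illustration only, since no loss rate is given, 115 evaluable per group gives 68% and 110 gives 66%.

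**The case against.** The strongest reply is that the documents never say two-sided. The hypothesis in section 4.1 is directional, and a one-sided 5% test yields exactly 122 from the stated inputs, with 81% power at 125 per group. On that reading the calculation is sound and only a word is missing. It can be added that the sentence on 95% intervals closes the paragraph on secondary outcomes.

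It is true that sidedness has to be inferred. But a directional hypothesis does not declare a one-sided test and is commonly paired with two-sided testing. The sentence on intervals covers all estimates, and the p < 0.05 threshold for the primary outcome carries no one-sided qualifier. Even if a one-sided test was meant, the text would still need correcting, because the test would have to be declared and the interval matched to it.

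A smaller point is that the exact match depends on using 103 h; with 102.3 h the one-sided answer is 120. This does not help the two-sided reading, since neither control value comes near 122 two-sided. It is also fair to say that the gap is modest in hours: the effect detectable with 80% power moves from 24 to about 26.

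**Conclusion.** The concern holds. The 122 per group belongs to a one-sided 5% test that is declared nowhere, and the analysis as described is two-sided. For that analysis the stated 80% power is about 71% with 125 evaluable per group (72% with 102.3 h as control) and 70% to 71% with 122. The chance of missing a true 24-hour reduction is about 29% instead of 20%. Reaching 80% would take 155 evaluable patients per group, 310 in total (152 and 304 with 102.3 h), before any withdrawals.

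This rests on the protocol's own mean, SD and effect, equal group sizes, and reading an unqualified p < 0.05 with 95% intervals as two-sided. It must be corrected because it is the sample-size justification for the primary endpoint and appears in two places.

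**What to change.** In the Synopsis (Statistical Methods) and section 8.2, replace the power sentence with one to this effect: with 125 evaluable patients per group and a two-sided 5% t-test on log10 length of stay, power is about 71% for a reduction from 103 to 79 hours, and 80% power corresponds to a reduction of about 26 hours. In section 8.3 and the statistical analysis plan, state that the primary test is two-sided. The word evaluable matters, because withdrawals and missing data lower the figure further.

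This costs a few words and no extra enrolment; the price is a less favourable stated power. There are two alternatives. The sponsor could keep 80% two-sided power by planning for about 155 evaluable per group. If a one-sided 5% test was what the sponsor intended before seeing any outcome data, the sponsor could declare it and report the matching 90% interval.
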